### Analysis of primary outcome

Change in weight at each measurement point will be analyzed by fitting a mixed-effects model for repeated measures. The explanatory variables of the model include the pre-pregnancy body weight, measurement time points, intervention group, and interaction between measurement time points and intervention group. The variance structure is unstructured (variance at each time point is heterogenous). Using this model, the least mean square of the rate of change in body weight at 12 months postpartum and its 95% confidence interval are estimated for each group, and differences between the groups are compared using t-tests (two-sided). The significance level of the test is set at 0.05.

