## Methods/Design

This protocol follows the SPIRIT guidelines [21]. SpringMom will be a multicenter randomized controlled trial in which participants will be randomly allocated to an intervention at each facility. The intervention will last until 1 year postpartum, and the participants will be observed until 2 years postpartum.

The enrollment period started in September 2020 and will end in June 2021, and the observation period started in September 2020 and will end in January 2024. Figure 1 shows the flow chart of the study procedures. This trial was approved by the ethics review board of the National Center for Child Health and Development, Tokyo, Japan.

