### Allocation

Randomization will be conducted on the site level, not on the patient level. Every day during the enrollment period before starting recruitment, the trial secretariat will perform central allocation with a random number table to decide whether to enroll the participants in the intervention or non-intervention group at each site and, subsequently, will inform every site.

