#### Health outcomes

✓ Pregnancy outcomes (gestational age at delivery, cesarean section rate, preterm birth rate, excessively large baby rate, birth height, birth weight, SD value, large-for-gestational-age rate, pregnancy-induced hypertension rate, gestational diabetes rate, etc.)Maternity checkup and pregnancy outcome data will be collected from the Maternal and Child Health Handbook.✓ Weight gain during pregnancy (kg)Calculated as: (weight immediately before delivery retrieved from the Maternal and Child Health Handbook)—(pre-pregnancy weight).✓ Change in weight from before pregnancy to 1, 6, 12, and 24 months postpartum (kg)✓ Rate of change in weight from before pregnancy to 1, 12, and 24 months postpartum (%)

The postpartum weights will be directly retrieved from the smartphone application as measured by the device.✓ Percentage of participants who will reach the target weight (at 6, 12, and 24 months postpartum) (%)A participant will be considered to have reached the postpartum target weight if/when their body weight declines to 93% of the weight before pregnancy.✓ Change in body fat ratio from 1 month postpartum to 6, 12, and 24 months postpartum✓ Percentage of participants with hypertension (excluding those having been diagnosed before pregnancy)The mean of the two blood pressure readings taken at home in the morning and before going to bed will be used. If only one blood pressure reading is taken, that value will be used. Hypertension is defined as a 3-day mean of ≥ 135 mmHg and/or ≥ 85 mmHg.✓ Percentage of participants with impaired glucose tolerance or diabetes (at 6, 12, and 24 months postpartum)Postpartum impaired glucose tolerance is defined as fasting blood glucose ≥ 110 mg/dl and ≤ 125 mg/dl or HbA1c ≥ 6.0% and ≤ 6.4% in the at-home blood samples. Diabetes is defined as a fasting blood glucose level of ≥ 126 mg/dl or HbA1c is ≥ 6.5%.✓ Percentage of participants with EPDS ≥ 9 (start of the study and at 1 month postpartum)

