### Analysis of secondary outcomes

For continuous variables, the mean and 95% confidence interval will be calculated for each group and t-tests will be used for group comparisons. For discrete variables, the number, proportion, and 95% confidence interval for the proportion will be calculated for each group, and the chi-square test will be used for group comparisons.

Regarding the breastfeeding proportion, ≥ 80% breastfeeding (daily milk amount ≤ 125 ml at 1 month postpartum and ≤ 164 ml at 6 months postpartum) will be used for between-group comparisons. Regarding the dietary items, the means and 95% confidence intervals will be calculated for each item at each time point (at the start of the study and 6 and 12 months postpartum) in the intervention group. The same analysis will be performed to analyze changes from the start of the study to 6 and 12 months postpartum.

For device usage, the use of activity tracker meters, wearing the weight/body composition monitor, and performance of measurements with the weight/body composition monitor at each time point (6 and 12 months postpartum) will be summarized and compared between the groups. In the group that will not use the devices at the beginning of the study, the number, proportion, and 95% confidence interval for the proportion will be calculated for participants who started using the devices at 6 and 12 months postpartum.

Regarding mobile application use, the mean and 95% confidence intervals will be calculated for the number of logins and viewing time at each time point in the intervention group (at 6 and 12 months postpartum). For uploading of meal images (at 6 and 12 months postpartum) and viewing of breastfeeding videos (during pregnancy and at 6 weeks postpartum), the number, proportion, and 95% confidence interval will be calculated for the intervention group.

Regarding the continuation of the intervention program (at 6 and 12 months postpartum), the number, proportion, and 95% confidence interval will be calculated for the intervention group.

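### Arms are drawn by site and day, but the stated analyses contain neither site nor site-day, and the primary model leaves out gestational age and weight at consent

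*Protocol article*

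**What the plan says.** On allocation, the protocol article says: "Randomization will be conducted on the site level, not on the patient level". The timing of the draw is given as "Every day during the enrollment period before starting recruitment". The secretariat makes it centrally, from a table of random numbers, and tells each site the result. No blocking or ratio is given. The Methods/Design section describes allocation differently: "participants will be randomly allocated to an intervention at each facility".

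On the primary analysis: "Change in weight at each measurement point will be analyzed by fitting a mixed-effects model for repeated measures". The section then names the model terms: "The explanatory variables of the model include the pre-pregnancy body weight, measurement time points, intervention group". A time-by-group term completes the list, and the covariance over time is unstructured. The same section asks for least-squares means of the rate of change at 12 months.

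On secondary outcomes: "For continuous variables, the mean and 95% confidence interval will be calculated for each group and t-tests will be used for group comparisons". Discrete outcomes get a chi-square test. Neither site nor a baseline value is mentioned.

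The Participants section requires less than 30 weeks of gestation and a weight below 120 kg when consent is given, so both values are known at entry for every woman.

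**The concern.** The analysis does not follow the allocation. If every woman recruited at one site on one day receives the same arm, the randomised unit on the natural reading is the site-day. The stated model and tests treat women as independently randomised.

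- **Site-day.** Correlation among women in the same site-day makes the ordinary standard error too small.
- **Site.** With an unblocked random number table, the arms can end up unevenly spread over four hospitals, and nothing in the model removes the resulting difference. If chance instead balances the arms within site, leaving site out makes the standard error slightly too large.
- **Weight change before allocation.** The outcome runs from pre-pregnancy weight, but a woman may join at any point up to 30 weeks. Weight change before entry cannot be an effect of the app. It stays in the outcome as noise unless weight and gestational age at consent are in the model.
- **Dependent variable.** The model is introduced as one for change in weight and then used to estimate the rate of change. The Health outcomes section lists change in kg and rate of change in % as separate outcomes, so the scale should be named.

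**Working it through.** **Inputs from the article.** Difference 3 percentage points (−2% against −5%), SD 8%, two-sided 5%, 80% power, 226 evaluable women in total, 270 registered, about 20% loss, four sites. The enrolment window is September 2020 to June 2021 in Methods/Design, and a 5-month registration period in Sample size.

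**Inputs that are assumptions.** 1:1 allocation. About 200 working days for ten months and 100 for five months, or about 22 recruiting days if a site recruits one day a week for five months. ICC within site-day 0.02 to 0.05. Correlation r of 0.2 to 0.5 between the consent-visit covariates and the 12-month % change. The article supports none of these ICC or r values.

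**Step 1: the plan's own figure.** Standardised difference 3/8 = 0.375. The two-sample t calculation gives 113 per arm, 226 in total, power 0.801. The stated 226 is reproduced exactly with no design effect, so the sample size treats women as independent.

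**Step 2: starting power.** 270 × 0.80 = 216 evaluable, 108 per arm: power 0.783.

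**Step 3: clustering on site-day.** Mean recruits per site-day λ = 270/(4 × days). For Poisson cluster sizes the size-weighted mean is 1 + λ, so the design effect is 1 + λ × ICC. Power uses 108/(design effect) per arm. The error rate of the naive test is 2 × [1 − Φ(1.96/√design effect)].

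| Recruiting days per site | λ | Design effect, ICC 0.02 to 0.05 | Power at 216 | Naive type I error |
|---|---|---|---|---|
| 200 (ten months, daily) | 0.34 | 1.007 to 1.017 | 0.781 to 0.777 | 0.051 to 0.052 |
| 100 (five months, daily) | 0.675 | 1.014 to 1.034 | 0.778 to 0.770 | 0.052 to 0.054 |
| 22 (five months, weekly) | 3.07 | 1.061 to 1.153 | 0.759 to 0.723 | 0.057 to 0.068 |

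**Step 4: simulated type I error.** 216 women, four equal sites, unblocked site-day allocation, 4,000 runs per scenario (Monte Carlo standard error √(0.05 × 0.95/4000) = 0.003). With 100 or 200 days per site the unadjusted test rejected in about 0.050 to 0.057 of runs, whether or not site or site-day effects were present. With 22 days it rejected in 0.064 to 0.076 when site effects, alone or with site-day effects, held 5 to 10% of the variance. Adding site brought this to 0.053 to 0.055 with site effects only, but left 0.059 when a site-day effect was also present. Site adjustment therefore does not replace site-day clustering.

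**Step 5: gain from consent-visit covariates.** Residual variance is multiplied by 1 − r², so the standardised difference becomes 0.375/√(1 − r²), with 108 per arm:

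| r | 1 − r² | Power at 216 |
|---|---|---|
| 0 | 1.00 | 0.783 |
| 0.2 | 0.96 | 0.800 |
| 0.3 | 0.91 | 0.820 |
| 0.5 | 0.75 | 0.886 |

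**The case against.** The case on the other side is substantial, and most of it limits the point.

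- **The primary model already has a baseline.** It adjusts for pre-pregnancy weight, the reference value of the outcome. A reader might infer that baseline is ignored altogether; it is not. What is missing is gestational age and weight at consent.
- **Clustering is small under the stated schedule.** Allocation is described as daily, the advice is automated and individual, and no shared session or therapist is described that would create correlation within a site-day. Counting only the 216 analysed women lowers the weekly worst case to λ = 216/88 = 2.45 and, at ICC 0.05, a design effect of 1.12. This stands.
- **Whole hospitals as clusters.** The Allocation wording tempts a reader to infer four clusters. With 226/4 = 56.5 women per site, an ICC of 0.02 would give a design effect of 1 + 55.5 × 0.02 = 2.11 and a sample of 477. The daily draw and the Methods/Design sentence, which places allocation within each facility, do not support that reading.
- **Baseline adjustment of secondary outcomes is limited.** EPDS is analysed as the proportion scoring 9 or more, so analysis of covariance does not fit. The intervention starts on the day of consent, so first-week steps and sleep may already reflect the app; adjusting for them could bias the comparison. Home blood pressure and postal blood tests have no baseline, and body fat change is referenced to one month postpartum.
- **Weights at other visits.** A reader might infer complete-case t-tests for these. The article does not say so; it sends weight at each measurement point to the repeated-measures model. The general t-test sentence for secondary outcomes only leaves it unclear which analysis governs.
- **The scale of the outcome.** The rest of the article defines the primary outcome as % change, so the mismatch is probably loose wording.
- **A condensed article.** The terms are introduced with a verb that leaves room for others, and a fuller plan may add site. The listed terms and tests are still the ones on record.

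**Conclusion.** The point holds in a limited form and is worth acting on. Allocation is by site and day without stated blocking, and the listed primary terms and secondary tests reflect neither. Two pre-intervention variables that eligibility already requires are unused, although part of the outcome precedes allocation.

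The documents do not support a claim that the intervals are seriously wrong. With near-daily allocation over ten months and ICC 0.02 to 0.05, the design effect is about 1.01 to 1.02 and power stays near 78%. Only concentrated recruitment, about one day a week for five months, takes it to about 1.06 to 1.15. The likely practical gain lies in the consent-visit covariates: from 78% to 80–89% at 216 women if r is 0.2 to 0.5. Both ranges rest on assumed values.

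**What to change.** 1. State the randomised unit plainly and reconcile the Allocation section with Methods/Design.
2. Fit the repeated-measures model explicitly to % change from pre-pregnancy weight. Keep the existing terms and add site as a fixed effect, gestational age at consent and weight at consent, the last measured before the app starts.
3. Use standard errors clustered on site-day, at least as a sensitivity analysis.
4. Take the 1-, 6- and 24-month % changes from the same model.
5. Adjust secondary comparisons for site. Analyse EPDS of 9 or more by logistic regression on site, adding the start-of-study score if it was taken before app exposure.
6. Do not adjust for first-week steps or sleep unless they are recorded before app exposure.

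The cost is wording, a few degrees of freedom and possibly slightly wider intervals. Gestational age and weight at consent are already known from the eligibility check. The change should be fixed before outcomes are seen by arm.

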### Data collection

All study participants must weigh themselves once at the start of the study and at 1, 6, 12, and 24 months postpartum and track their activity and sleep patterns for 1 week at the beginning of the study and at 6, 12, and 24 months postpartum. Body weight will be measured once a day in the morning using the weight and body composition monitor. Activity and sleep will be measured using an activity and sleep tracker, which will be worn on the non-dominant arm at all times, even during sleep, except during recharging (once every 5 days).

All participants will complete online questionnaires at the beginning of the study and at 1, 6, and 12 months postpartum. If any data are lacking, they will be collected from the medical records. Details of the questionnaires developed for this study are as follows (supplementary file):

Background and lifestyle (at the start of the study): items related to pregnancy and delivery history, medical history, family history, and exercise and dietary habits.Edinburgh Postnatal Depression Score (EPDS) (start of study, 1 month postpartum) [22].Breastfeeding status (intensity, duration) questionnaire (1, 6, 12 months postpartum).Breastfeeding process questionnaire (1 month postpartum).Behavioral changes (attitude, knowledge) (6, 12 months postpartum).User-friendliness of devices, barriers to lifestyle improvements and behavioral changes, areas for improvement, etc. (6, 12 months postpartum) (both groups).Desire to continue using the IoT devices after the trial ends (12 months postpartum) (intervention group only).

All participants will have blood samples taken at home via postal self-checkups at 6, 12, and 24 months postpartum to measure HbA1c, fasting glucose, total protein, albumin, AST, ALT, γ-GTP, total cholesterol, HDL cholesterol, triglycerides, urea nitrogen, creatinine, and uric acid. To collect blood samples, the trial secretariat will send test kits to the participants for postal self-checkups. Results of the postal self-checkups will be returned by mail to the participants within 6 weeks.

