### Primary outcome

The primary outcome will be the ratio of change in body weight (%) from pre-pregnancy to 12 months postpartum.

The pre-pregnancy weight will be self-reported, as weights reported by obese individuals have been reported to differ only slightly from actual measurements. The body weight at 12 months postpartum will be directly retrieved from the smartphone application as measured by the device.

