### Sample size

Assuming a -2% weight change at 12 months postpartum compared to before pregnancy in the non-intervention group, the trial was designed to detect whether the IoT/mobile application intervention would result in a -5% weight change at 12 months postpartum. To conduct a two-sided test with a standard deviation of 8% and significance level of 5% at 80% power, 226 participants in both groups are needed. Assuming loss of approximately 20% of participants from exclusion or drop-out, the target number of registrations is set to 270 women.

There are 6,000 deliveries each year at the trial institutions. If 10% of the women are obese, the total number comes to 600 per year. As pregnant women at up to 30 weeks of gestation are eligible for registration, 250 pregnant women at up to 30 weeks of gestation who have already visited the outpatient maternity clinic for checkups and 250 pregnant women who newly visit during the 5-month registration period will be eligible. Hence, it is expected to be possible to register the target number of participants.

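### The primary repeated-measures model gives pre-pregnancy weight one slope at every postpartum visit; a weight-by-visit term would guard the 12-month comparison against some loss of precision and, under one dropout pattern, bias

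*Protocol article*

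**What the plan says.** The article's section on the analysis of the primary outcome specifies a mixed-effects model for repeated measures. Its main effects are given as follows: "The explanatory variables of the model include the pre-pregnancy body weight, measurement time points, intervention group". The only interaction that the section names is the "interaction between measurement time points and intervention group". The covariance is unstructured, with a separate variance at each visit. The fit then yields, for each arm, an adjusted mean percentage change at 12 months with a 95% confidence interval, and the arms are compared at that visit by a two-sided t-test at 0.05.

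The section on the primary outcome defines the endpoint: "The primary outcome will be the ratio of change in body weight (%) from pre-pregnancy to 12 months postpartum". The section on data collection sets the weighing schedule: "All study participants must weigh themselves once at the start of the study and at 1, 6, 12, and 24 months postpartum". The model could therefore span three postpartum visits (1, 6 and 12 months) or four (with 24 months). The article gives no slope or correlation between pre-pregnancy weight and later weight change at any visit.

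**The concern.** The model is flexible by visit in two respects, the group effect and the covariance, but not in the covariate. Weight at 1 month postpartum may largely reflect what remains of gestational gain, and weight at 12 months longer-term weight control. It would be unsurprising if pre-pregnancy weight related differently to the two. A common slope is then a compromise across visits and may fit 12 months, the visit that decides the trial, worse than its own slope would.

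Two things are at stake. First, variation that the covariate could explain at 12 months stays in the residual and widens the confidence interval. Second, a wrong slope at 12 months adjusts wrongly for any difference between arms in the starting weight of the women still observed. That matters if dropout depends on pre-pregnancy weight in a different way in each arm.

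**Working it through.** **The plan's own figure.** The article's sample-size section gives means of −2% and −5%, SD 8%, two-sided 5%, power 80%, and 226 women in total. By the normal approximation, n per arm = 2 × (1.960 + 0.842)² × 8² / 3² = 111.6, so 112 per arm or 224. The noncentral-t calculation gives 113 per arm, or 226, which matches. (Equal allocation is assumed.) The SD is unadjusted, so the calculation takes no credit for the covariate. At 113 per arm the normal-approximation power is 80.5%.

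**Formula for precision.** Let X be pre-pregnancy weight in SD units, b12 its true slope at 12 months, bc the common slope that maximum likelihood settles on under an unstructured covariance, and s² the 12-month variance left after visit-specific adjustment. With complete data, the variance of the 12-month contrast under the common slope, relative to visit-specific slopes, is

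ratio = 1 + (b12 − bc)² / s².

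**Inputs not in the documents.** These are assumed: correlations of weight change with X at 1/6/12 months as in the table, visit SDs of 6/7/8 or 8/8/8, and residual correlation between visits of 0.5 to 0.85. The SD of 8 at 12 months is the plan's own.

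**Worked case.** Take correlations 0/−0.15/−0.3, SDs 6/7/8 and residual correlation 0.7. Then b12 = −0.3 × 8 = −2.4, bc = −0.66, and s² = 64 × (1 − 0.09) = 58.24. The ratio is 1 + (−2.4 + 0.66)² / 58.24 = 1 + 3.03/58.24 = 1.052, worth 0.052 × 226 ≈ 12 women. Power is 82.1% with the common slope and 84.0% with visit-specific slopes.

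| Correlations at 1/6/12 months | Variance ratio | Power, common slope | Power, visit-specific |
|---|---|---|---|
| 0 / 0 / 0 | 1.000 | 80.5% | 80.5% |
| −0.2 at each visit | 1.000–1.002 | 82.0% | 82.0% |
| 0 / −0.1 / −0.2 (mild) | 1.009–1.036 | 80.7–81.7% | 82.0% |
| 0 / −0.15 / −0.3 (moderate) | 1.017–1.079 | 81.2–83.4% | 84.0% |
| 0 / −0.2 / −0.4 (strong) | 1.023–1.133 | 82.4–86.0% | 86.8% |
| +0.2 / 0 / −0.2 (strong) | 1.042–1.117 | 77.7–80.5% | 82.0% |
| −0.4 / −0.2 / 0 (strong) | 1.048–1.099 | 76.7–78.6% | 80.5% |

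In the last row pre-pregnancy weight has no relation to the outcome at 12 months, so the common slope adjusts for something that is not there. Its variance is then up to 1.10 times that of no adjustment at all.

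**Check by simulation.** With 600 trials per scenario, 270 randomised and 16.3% missing at 12 months, the ratio of standard errors (common to visit-specific) was 1.000 with no association and 1.001 with equal correlations. It was 1.013, 1.030 and 1.053 for the mild, moderate and first strong patterns. Squared, the last three are 1.026, 1.061 and 1.109, all inside the table's ranges. Both models averaged about −3, the true difference.

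**Bias under dropout.** A further simulation used 400 trials per scenario, 270 randomised, SDs 6/7/8, roughly 15–20% missing at 12 months and a true effect of −3. The two figures in each cell are for the mild and moderate patterns.

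| Dropout by pre-pregnancy weight | Common slope | Visit-specific slopes |
|---|---|---|
| Equal in both arms | no bias | no bias |
| Intervention arm only | −2.78, −2.69 | −2.97, −3.00 |
| Opposite directions in the two arms | −2.59, −2.46 | −2.98, −3.01 |

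The effect shrinks by 0.22/3 = 7% to 0.54/3 = 18%. The standard error in one trial is about 8 × √(2/113) = 1.06, so a mean over 400 trials has a Monte Carlo error of about 1.06/20 = 0.05. The common-slope shifts exceed that clearly; the visit-specific departures do not. Missingness here depends only on an observed covariate, so it is missing at random; the bias comes from the misfitted slope. Its size and sign follow from the assumed slopes and dropout: reversing the direction of dropout would push the estimate away from zero instead.

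**Cost.** With two added parameters the critical t moves from 1.97066 (223 df) to 1.97076 (221 df).

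**The case against.** The strongest case against is that this is a condensed article. It says that the explanatory variables include certain terms, which need not be a complete list, and a covariate-by-visit term is a detail that an analysis plan often settles. That stands in part: the full plan may already contain the term. But the article does choose to list the fixed effects and names one interaction, so the natural reading is that no other is planned.

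A second objection is that nothing in the documents shows that slopes differ by visit. The endpoint is a percentage already scaled by pre-pregnancy weight, which may weaken the association. This stands. A reader might infer that the model as written certainly loses precision; the documents do not support that, because with equal or null slopes the loss is zero.

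Third, under randomisation and with dropout unrelated to weight, or related to it alike in both arms, the contrast is unbiased. This also stands. A reader might infer that the primary result will be biased, but the article says nothing about how dropout relates to weight. Participants are unblinded and only the intervention arm has daily self-monitoring and meal entry, so different dropout by arm is plausible, but no more than that.

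**Conclusion.** The point holds in a limited, conditional form. As written, the model imposes a common slope for pre-pregnancy weight. If the true slopes differ, the variance at 12 months is inflated by about 1–8% under mild to moderate differences and by up to about 13% under strong ones; otherwise by nothing. In the strong cases the loss is about 1 to 4 power points. Bias needs two conditions together: slopes that differ by visit, and dropout that depends on pre-pregnancy weight differently by arm. In the cases simulated it moved a true −3 to between −2.46 and −2.78. All of these sizes rest on assumed correlations, visit SDs and dropout patterns.

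A reader might also infer that the missing term undermines the planned 80% power or makes the enrolment target too small. The documents do not support this. The 226 rests on an unadjusted SD, and power falls below plan only where the common slope fits 12 months worse than no adjustment. Whether the enrolment target allows enough for losses is a separate question that this term does not cause. A common slope is a legitimate specification, and the change is a minor improvement.

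**What to change.** In the section on the analysis of the primary outcome, add pre-pregnancy body weight × measurement time point to the explanatory variables, before any unblinded analysis. If the full analysis plan already has this term, one clarifying phrase is enough. The cost is two extra parameters if the model uses 1, 6 and 12 months, or three if it also uses 24 months. No new data are needed, because the covariate is already in the model.
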